### Recruitment and eligibility

The 2GO-CGM trial will enrol 80 participants, aged 16 years and older with T2D. Participants will be recruited from Waikato, Canterbury and Southern regions, collectively servicing approximately 65,000 people with T2D [30]. To be eligible, participants must have a sub-optimal Hba1c (HbA1c > 8.0% or 64 mmol/mol) despite receiving at least 0.2 units of insulin per kilogram, per day, for at least 3 months prior to study enrolment. Full eligibility criteria are presented in Table 2. While not an eligibility criterion, it is expected that most participants will be rtCGM naïve, given that rtCGM is currently unfunded and therefore not widely used by people with T2D in New Zealand.

**Table 2 Tab2:** Eligibility criteria for participation in the 2GOCGM study

Inclusion criteria	Exclusion criteria
• Type 2 diabetes as per American Diabetes Association classification • HbA1c >8.0% or 64 mmol/mol • Minimum daily insulin use of ≥0.2 units of insulin/kg/day for >3 months • Aged 16 years and over • Be willing and able to conform to the study protocol • Have access to a smartphone or computer with internet connection	• History of type 1 diabetes • History of other types of diabetes such as diabetes secondary to pancreatitis • Has had a hospital admission for hyperglycaemia in last 6 months • Use of systemic corticosteroids >14 days, or repeated pharmacologic systemic courses of corticosteroids • Recurrent or chronic systemic infections that, in the view of the investigator, would significantly impact on glycaemia. • Major cardiovascular event or major surgery in last 3 months • Active malignancy requiring ongoing treatment • Previous or planned bariatric surgery • Pregnancy, or plan to become pregnant while participating in study • Any other reason that investigator feels may not be in best interest of patient to participate

Māori are the tāngata whenua (indigenous people) of New Zealand and are disproportionately affected by T2D. Māori are an underrepresented population in both CGM use and research, and recruitment of Māori people will be prioritised for the study group to be representative of the T2D population in New Zealand.

Potential study candidates will be identified by their local healthcare professionals (e.g. general practitioners, practice nurses and specialist diabetes clinicians) and agree to be phoned by a study team member for more information about the study and to confirm eligibility. Māori and Pacific participants may prefer an initial face to face appointment for *whakawhānaungatanga* (making a connection with research team member/s) before discussing the study and eligibility [31] and will be offered this opportunity. Potential participants will be given adequate time to review the patient information and consent form (PCIF) before indicating whether they would like to join the study. Processes of obtaining formal consent will meet the requirements of ISO 14155:2011 and Good Clinical Practice. Participants will confirm consent at the first screening appointment (Day 0) where they will provide written informed consent before any study specific assessments are performed. Additional consent will be sought for participation in interviews regarding the use of the Dexcom G6/G7 system. Table 3 shows the baseline information that will be collected once consent has been obtained and the participant has been screened, confirmed as eligible and enrolled into the study.

**Table 3 Tab3:** Baseline assessments for 2GO-CGM study

Demographic	Date of birth Ethnicity Gender
Anthropometric	Height Weight Body Mass Index (BMI) Seated blood pressure, recorded as average of 2 measurements at least 5 minutes apart
Diabetes	Date of diagnosis HbA1c (local laboratory value taken within the last 30 days) Number of episodes of severe hypoglycaemia, defined as coma or convulsion requiring assistance from others, in the 12 months prior to baseline visit. Number of hospitalisations in the last 12 months (diabetes and non-diabetes related)
Clinical	Medical history, including co-morbidities Medication list Known allergies Results of retinal screening within past 24 months (if not done, retinal photography will be arranged) Insulin injection sites checked for lipohypertrophy Check of insulin management and injection techniques
Lifestyle	Smoking status, alcohol, recreational drug use
Laboratory	Fasting glucose Fasting lipid profile Full Blood Count Liver function tests (AST and ALT) Estimated glomerular filtration rate High-sensitivity C-reactive protein Urine albumin creatinine ratio

### Sample size and power calculation

In a recent study examining intermittent CGM in a population with type 2 diabetes, baseline time in range (TIR) was 62.5% ± 20% [32]. Our inclusion criteria predicts a population that are likely to have lower time in range, which we estimate at 56% ± 20%. To detect a difference to a mean improvement of 14% TIR (to the target TIR of 70% set by international guidelines), at 80% power and α of 0.05, we would need 33 participants in each arm. The sample size has been inflated to 40 participants in each arm to account for possible loss-to-follow-up. This power calculation is a conservative estimate, and we are likely to be able to detect a smaller difference. For example, adjusted for baseline TIR a sample size of 40 per group will give 78% power to detect a difference of 10% TIR, assuming a within-person standard deviation of 18.5% (correlation coefficient of r = 0.58) [32], and that there is no loss-to-follow-up. The mean between-group difference in TIR at 12 weeks will be estimated with 95% confidence intervals using analysis of covariance, a general linear model that adjusts for TIR at baseline.

### Randomisation

The 2GO-CGM participants will be randomly allocated to use Dexcom G6 CGM or routine care with CareSens Premier meter with an allocation ratio of 1:1. The study statistician will prepare a computer-generated randomisation list with permutated blocks of random size.

The randomisation list will be stratified by:Use of metformin (Yes/No)Use of SGLTi or GLP agonist (Yes/No)

Use of this stratification plan is based on recent public funding for SGLTi and GLP agonists as second-line agents in New Zealand. Given this recent change these agents have not been widely used and therefore participants will be randomised based on prior use of either agent on entry to the study.

The randomisation list will be loaded into the REDCap (Research Data Capture) database by the study statistician immediately prior to moving the project to production status. Once the project is moved to production, the randomisation list is locked and becomes unmodifiable and inaccessible to the study team, thereby preserving allocation concealment. The study statistician will not be involved in participant enrolment. Patients who give consent for participation, meet the eligibility criteria, and are enrolled in the study, will be given a unique study identifier. After stratification variables have been entered into REDCap, research staff with authorisation to randomise participants may click the ‘randomise’ button, which will assign the treatment to the study number according to the next allocation on the randomisation list. This process will lock the fields containing the treatment group and stratification variables. Blinding will not be possible due to the nature of the technology.

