## Methods

### Study design

This multi-centre, randomised controlled trial (RCT) of 80 participants will be conducted in Aotearoa New Zealand over a period of 14 weeks, including a 2-week run-in period for blinded CGM data to be collected from all participants. Following the 2-week run-in period, participants will be randomised 1:1 to either the rtCGM intervention arm (Dexcom G6 rtCGM system (Dexcom Inc., San Diego, CA)) or the control arm (SMBG) with a CareSens premier meter (i-SENS Inc., Seoul, Korea)) for a period of 12 weeks. The primary endpoint will be measured in the final two weeks of the RCT phase (week 10–12), with blinded rtCGM data collected from the control group and compared with unblinded rtCGM data from the intervention group. The 12-week RCT phase will be followed by a continuation phase, where those initially randomised to routine care will cross over into the rtCGM intervention for a further 12 weeks. Following this, participants will be invited to join the extension phase of this study and continue rtCGM use for a further 12 months. As such, the expected duration of subject participation is 78 weeks. At least five visits to the study centre and six ‘remote reviews’ are planned for participants over the study duration (see Table 1). During the 12-month extension phase participants will switch from using the Dexcom G6 system to the Dexcom G7 system, once available.

**Table 1 Tab1:** 2GO-CGM study schedule of assessments

	Baseline	Run-in period 14 days	Treatment period week 1–12				Continuation PERIOD Week 12–24			EXTENSION PERIOD Week 25–77			
	Clinic visit		Clinic visit day 1	Remote review week 2, 8	Week 10–12	Clinic visit end of study week 12	Clinic visit week 12	Remote review week 14, 20	Clinic visit end of study week 24	Week 38 remote review	Clinic visit week 51	Week 64 remote review	Clinic visit end of extension study week 77
Informed consent	X								X				
Demographics	X												
HbA1c Height, weight, BMI	X		X			X	X		X		X		X
Medical review	X					X	X		X		X		X
Blood pressure	X					X	X		X		X		X
Urine pregnancy test	X												
Fasting lipids, FBC, glucose, LFTS, eGFR	X					X	X		X		X		X
Urine ACR	X					X	X		X		X		X
Blinded CGM (14 days)		X			X (control arm)								
Return to clinic after 7 days of blinded CGM for new sensor		X			X (control arm)								
CGM training			X				X						
Electronic review				X				X		X		X	
AE collection		X	X	X		X	X	X	X	X	X	X	X
Sleep quality		X				X							
Food diary		X				X					X		

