### Blinded rtCGM

All participants will have at least 10 days of glucose data recorded by blinded Dexcom G6 device in the 2-week run-in phase of the trial. This data will be used by prescribing diabetes nurse specialists (DNS) to maximise non-insulin glucose lowering medications for all participants prior to randomisation into study group.

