### Run-in phase

During the run-in phase prescribing DNS will adjust non-insulin glucose lowering medications with the aim to maximise these medications prior to the RCT phase for all study participants. DNS will also assess cardiovascular risk factors and adjust anti-hypertensive and lipid lowering medications in the run-in phase and continuation phase, based on national guidelines [34].

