### Statistical analysis

Statistical analysis will be performed using up-to-date specialist software (R or Stata). Analysis will follow the intention-to-treat principle, with all participants who commence the RCT phase included in the data set as randomised. Two-sided P-values will be reported, with an alpha of 0.05 considered statistically significant. The type 1 error for primary and secondary efficacy outcomes will be controlled using an ordered testing procedure where formal testing stops as soon as a non-significant result (p > = 0.05) is observed. Analysis of secondary exploratory outcomes will use the two-stage Benjamini-Hochberg method to control the false discovery rate.

Real-time CGM data will be collected in the run-in phase and week 10–12 of the RCT phase and used for calculation of baseline and follow-up CGM metrics, respectively. Participant CGM metrics will only be set to missing if less than 24 hours of data has been collected. The primary endpoint (TIR 3.9–10.0 mmol/L; 70- 180 mg/dL) will be calculated for each participant by dividing the number of CGM measures in target range, by total number of CGM values recorded. The overall treatment effect (primary outcome) will be determined by fitting an ordinary least squares linear regression model with percentage time in target glucose range at 12 weeks as the dependent variable and treatment group as the independent variable. The model will adjust for stratification variables (baseline use of metformin and use of SGLTi or GLP agonist) and percentage time in target glucose range during the last two weeks of run-in. This model will be used to calculate point estimate, 95% profile likelihood confidence intervals, and p values for the treatment group difference at follow-up. Continuous secondary endpoints (e.g CGM metrics, anthropometric, clinical and laboratory cardiovascular measures and PSQI) will follow the same approach as described for the primary efficacy endpoint.

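### Drugs newly started in the run-in are balanced only by chance and only partly adjusted for, because strata and covariates use drug status at study entry: a loss of precision, not a bias

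*Protocol article*

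**What the plan says.** **Protocol article, Study design:** randomisation comes after the run-in: "Following the 2-week run-in period, participants will be randomised 1:1".

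**Randomisation:** the two strata are metformin use and SGLTi or GLP agonist use, each yes or no. For the second, "participants will be randomised based on prior use of either agent on entry to the study". The stated reason is that these agents were only recently funded and not yet widely used. The stratum fields are entered into REDCap before the allocation is requested, and are then locked.

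**Blinded rtCGM and Run-in phase:** the nurse specialists will "adjust non-insulin glucose lowering medications with the aim to maximise these medications prior to the RCT phase for all study participants". At least 10 days of blinded run-in data inform this.

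**Randomised controlled trial phase:** after randomisation only insulin is changed, except for safety.

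**Statistical analysis:** "The model will adjust for stratification variables (baseline use of metformin and use of SGLTi or GLP agonist" and for "percentage time in target glucose range during the last two weeks of run-in". No stated covariate records a drug started during the run-in.

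**The concern.** The stratum and the covariate describe a drug status that the protocol sets out to change before allocation. Non-insulin drugs are then largely held fixed until the week 10-12 endpoint. The regimen after the run-in is thus the one that acts on the outcome, while the model carries the regimen before it.

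The non-user stratum can then mix people about to benefit from a new drug with people who are not. On the protocol's own reasoning, that the agents are not widely used, this is likely to be the larger stratum. Baseline TIR does not separate the two groups well, because the drug changes are guided by the same window that supplies the baseline value. A predictor of week-12 TIR that is known before randomisation is left to chance balance and residual noise, in a trial of 80 people.

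The time point is also loosely worded. Randomisation says study entry, Statistical analysis says baseline, and the fields are completed just before allocation, after the run-in. Staff at three sites could code a newly started participant either way.

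**Working it through.** **1. The plan's own figures** (Sample size and power calculation). SD 20, difference 14, 80% power, two-sided 0.05:

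n per arm = 2 × (1.960 + 0.842)² × 20² / 14² = 32.04, rounded up to 33. This matches the plan.

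With r = 0.58, residual SD = 20 × √(1 − 0.58²) = 16.29, so residual variance is 265.4. For 40 per arm and 10 points, SE = 16.29 × √(2/40) = 3.64, and power = Φ(10/3.64 − 1.96) = 78%. This also matches. (The stated within-person SD of 18.5 is close to the SD of change, 20 × √(2 × 0.42) = 18.3, and is not needed here.)

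With 33 per arm analysed, the t-based power for 10 points is 68.9%. This is the reference value below.

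**2. Variance left by unrecorded new starts.** Let m be the share of non-users at entry, s the share of them started in the run-in, and e the drug's effect on TIR not yet visible at baseline. The documents give none of these, so all three are assumptions. The model already adjusts for entry status, so only the spread within the non-user stratum remains:

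added variance = e² × m × s × (1 − s)

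This is taken as additional to 265.4. If the planning SD of 20 already contains part of it, the loss against the plan is smaller.

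SD of the shift in the treatment estimate from chance imbalance = √(added variance × 2/33).

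| e | m | s | Added variance | Rise in residual variance | SD of shift (points) | Power, 33 per arm |
|---|---|---|---|---|---|---|
| 5 | 0.6 | 0.8 | 25 × 0.6 × 0.16 = 2.4 | 0.9% | 0.4 | 68.5% |
| 10 | 0.7 | 0.5 | 100 × 0.7 × 0.25 = 17.5 | 6.6% | 1.0 | 66.2% |
| 15 | 0.8 | 0.5 | 225 × 0.8 × 0.25 = 45.0 | 17.0% | 1.7 | 62.1% |
| any | any | 1.0 | 0 | 0% | 0 | 68.9% |

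The first and third rows are the extremes over m = 0.6-0.8, s = 0.3-0.8 and e = 5-15.

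**3. Bias and type I error, by simulation.** The setup was 80 participants, permuted blocks within entry-status strata, and the model adjusted for baseline TIR and entry status. Assumed values were 20-40% users at entry, 30-100% of non-users started, and an effect of 5-10 points. There were 4,000 runs per scenario, and metformin was left out.

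- For a true difference of 10 the mean estimate was 9.9-10.1.
- Type I error was 4.8% in the one null scenario run.
- Mean imbalance in new starters was 0. The 95th percentile of absolute imbalance was about 15-20 percentage points when 30-80% of non-users start, and 3-4 when all do.
- Adding a new-start covariate raised power by about 2.4 points at most (75.1% to 77.5%), and by nothing when all non-users start.

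**The case against.** The strongest reply is that nothing invalid has been planned. Optimising drugs before randomisation is deliberate, and the Discussion gives it as a way to reduce bias. Prior use is a reasoned stratifier, and adjusting for the strata plus baseline TIR is standard. This stands.

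A reader might infer that new starts are neither balanced nor adjusted for, and that the treatment estimate is therefore biased. The documents do not support that. A start made before allocation is a pre-randomisation characteristic, so it is balanced in expectation, and the confidence interval already reflects chance imbalance. Entry status also identifies part of the group: the more non-users are started, the closer the non-user stratum comes to being the new-start group itself.

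Nor should the size be computed as if the stratum did no work. With half of all participants started and a 15-point effect, that would give 15² × 0.25 = 56.25, a 21% rise in variance. That figure applies only if nobody uses an agent at entry.

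The upper end of the range also needs a drug effect of 15 points, more than the 14-point improvement the trial is designed to detect. At 5 points the loss of power is under one percentage point.

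It can also be said that supportive analyses belong in an analysis plan that is not shown. That is fair for a sensitivity analysis. But the article itself fixes the primary model's covariates and the time point of the stratum, and the point is about what it fixes.

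**Conclusion.** The point holds as a matter of precision and clarity. Drug status is fixed at entry, deliberately changed in the run-in, and then used in its superseded form in the model. New starts are balanced only by chance and only partly adjusted for. The analysis remains unbiased and keeps its type I error.

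Under the assumed ranges (60-80% non-users, 30-80% of them started, effect 5-15 TIR points, 33 per arm) residual variance rises by about 1-17%. Power for a 10-point difference is about 62-69% against 69%. If all non-users start, nothing is lost on this account. The true position in that range cannot be known from the documents, which give neither a start rate nor a drug effect. It could be negligible.

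What makes it worth acting on is the low cost, and the fact that allocation is not blinded: adjusting later for an imbalance that has become visible would look post hoc.

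**What to change.** 1. State that the stratification variables refer to study entry, and use that one time point in both Randomisation and Statistical analysis. Keep both variables in the model as randomised. The locked list need not change.
2. Before the allocation is requested in REDCap, record whether an SGLTi or GLP agonist was newly started in the run-in (yes/no) and, separately, whether metformin was.
3. Prespecify these indicators as additional covariates in the primary model and the continuous secondary models, or at minimum in a sensitivity analysis.

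The indicators should be added to the strata and not replace them. A single three-level variable (on at entry, started or increased in run-in, neither) has overlapping levels for someone on an agent at entry whose treatment is then increased. Used as a replacement, it could drop the factor on which allocation was stratified.

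**Cost:** one REDCap field per drug group and one or two degrees of freedom. The schedule of assessments lists the medical review at baseline and week 12 but not on day 1, so the entry must be added to the randomisation step. The net gain is negligible if the drug effect is small or nearly all non-users start.

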## Baseline measures

### Demographics

Demographic data (age, gender and ethnicity) will be collected from participants. Home addresses will be used to assess socioeconomic deprivation scores using NZDep2018. NZdep2018 is an area-based measure of deprivation, based on New Zealand census data [33]. Deprivation deciles between one and 10 are allocated to areas of approximately 100–200 people: decile one representing areas with the lowest deprivation scores and decile 10 representing areas of highest deprivation.

### Anthropometric

Investigative staff members will collect anthropometric measurements (height and weight) using calibrated instruments and standard clinical procedures. Weight will be measured to the nearest 0.1 kg, with shoes and heavy clothing removed. Height will be measured to the nearest 0.5 cm. Height and weight will be used to measure body mass index (BMI) using standardised formula.

### Clinical characteristics

Blood pressure will be measured in seated position with an appropriately sized cuff. Two blood pressure measurements will be taken at least 5 minutes apart at each review point and the average of both measures recorded.

Retinal screening results completed in the last 2 years will be recorded, or the participant will be referred for screening if no result is available. Medical history including diabetes-related complications and a complete list of medications will be recorded at baseline.

### Blinded rtCGM

All participants will have at least 10 days of glucose data recorded by blinded Dexcom G6 device in the 2-week run-in phase of the trial. This data will be used by prescribing diabetes nurse specialists (DNS) to maximise non-insulin glucose lowering medications for all participants prior to randomisation into study group.

## Study groups

### Intervention arm (Dexcom G6 system)

At the beginning of the RCT phase, participants randomised to the intervention arm will receive training on the Dexcom G6 system (Dexcom Inc., San Diego, CA) by investigative staff. Training will include: application and activation of the G6 system, setting and responding to alarms/alerts, interpreting arrows and trend graphs, using the share/follow function (if applicable) and calibration (if indicated).

Participants will have the Dexcom G6 app downloaded onto their compatible smartphone or will use a Dexcom receiver. Participants will also use Dexcom Clarity; glucose depository software which allows participants and investigative staff to view glucose data, and patterns, trends, and statistics. Participants will have individual Dexcom Clarity accounts, identifiable only by their study ID. Data from these accounts will be shared with the study team Dexcom Clarity Professional account, allowing for remote review of participant data by investigative staff.

For participants using Dexcom G6 app on their smartphone, the Dexcom Clarity app will also be downloaded onto their phone and data will automatically upload to Dexcom clarity when connected to the internet. Participants using the Dexcom receiver will upload their glucose data manually to the Dexcom Clarity website at least once every 30 days, and prior to review points.

